### Sample size calculation

The RCT comprises nomothetic (between-person) and idiographic (within-person) aspects. The nomothetic aspect of the study is captured by questionnaire data (e.g. self-reports on depressive symptoms), which will be used for group-based analyses (e.g. tests of efficacy). The idiographic aspect is captured by the ESM measurements, which are used to provide participants with personalized feedback. These two different types of quantitative analyses require different sample size calculations.

#### Group analyses

In the previous RCT, IDS-SR scores for the experimental group (ESM + feedback) showed an initial 3-point drop 8 weeks after baseline, which increased to a 10-point drop compared to baseline at 32 weeks [15]. With a sample size of 40 per group, an alpha of 0.05 and an intraclass correlation of 0.6 (between pre and post repeated measurements) we would have 85–99% power to detect a 3–10 point difference in IDS-SR score between each of our experimental groups compared to the control group [45]. In the previous RCT, about 10% of the enrolled participants withdrew prematurely or only completed the ESM study partially [15]. Given that our study has less face-to-face contact, commitment to the study protocol might be lower in our sample. To ensure we will have 120 participants who completed the study randomized over three conditions, we will enroll 150 participants in the study (i.e., 50 per study arm).

#### Within-person analyses

Participants allocated to one of the two ESM modules will record data using their smartphone five times a day for 28 days in their natural environment (*N* = 140 measurements). This will provide ample data for the feedback reports, which will mainly comprise descriptive statistics and graphs (e.g., on daily fluctuations in mood and week-by-week changes in average PA and NA). VAR modeling will be used to provide participants feedback on temporal relationships between variables (e.g., PA and physical activity). Exact sample size calculations are not possible in studies using VAR, as it is typically unclear in such studies what effect size can be expected. This is because analyses are personalized and the direction of causality and the number of lagged influences in the system under investigation are usually unknown [29]. However, previous work from our and other groups suggests that a number of 60–90 measurements is sufficient to reliably identify reciprocal associations between variables (e.g., [12, 13, 46]).

#### Qualitative analyses

Qualitative data will be collected through in-depth individual interviews. The aim of the interviews is to provide viewpoints on the added value of the ESM-modules based on participants′ personal experiences. Data collection will be continued until no new themes emerge from the data (data saturation procedure); for our confined research question the estimated sample size is ~ 8–10 participants per module [47].

### Statistical analyses

#### Efficacy of the ESM-modules

The data have a hierarchical structure, because multiple IDS-SR assessments will be clustered within participants. Therefore, multilevel regression analyses will be used with the two-way interaction between time (in weeks) and treatment allocation as fixed effects, participants as random intercept and a (linear or quadratic) random slope for time (similar to [15]). This way, we can examine the effect of time on depressive symptoms (across 6 IDS-SR measurements), the effect of group (3 levels: Do-module, Think-module, Control), and the interaction between time and group separately. Similar analyses will be performed to investigate the impact of the ESM-modules on empowerment (NEL) and functioning (OQ-45). In order to take into account individual differences regarding the time interval between the start date of the participation in ZELF-i and the start date of the treatment at the mental health organization, a covariate “start date treatment – start date ZELF-i” will be included in the analyses. Thresholds for statistical significance will be set at *p* < .05.

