### Participants

We will recruit 150 male and female adult patients referred for depressive complaints to general or specialized outpatient teams at mental health care organizations in the North of the Netherlands. Participants will be recruited within the research network of mental health institutions in the North of The Netherlands, the Rob Giel Research Center (https://www.rgoc.nl), which covers a catchment area of over 4 million inhabitants. Eligibility criteria are broad to include typical patients. Inclusion criteria are: a) indication for depression treatment by the mental health care professional (hereafter named: practitioner); b) age between 18 and 65 years; and c) written informed consent. Exclusion criteria are (based on practitioners’ appraisals): a) crisis intervention warranted (i.e., in the case of acute suicidality); b) presence of psychotic or manic symptoms; and c) incapability of following research procedures due to inadequate Dutch language proficiency, significant auditory or visual impairments or mental retardation. Patients will be enrolled in regular treatment upon availability, that is, the start of regular treatment will not be postponed until participation in ZELF-i finishes. The ZELF-i intervention is intended as an add-on tool at the start of care as usual and thus circumstances are otherwise kept as ‘natural’ as possible. Participants will receive travel reimbursements and an additional €10 if they used the data bundle of their own smartphone to participate in the intervention.

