#### Introduction session and baseline measurement

The introduction session will take place at the mental health care organization. At the start of the introduction session, participants will have another opportunity to ask questions about the study procedures. If everything is clear, they will be asked to provide written informed consent. After the informed consent procedure, participants will be randomly allocated to the control group or one of two ESM intervention groups. Then, detailed instructions and practice runs for the ESM modules follow, depending on the allocated treatment condition. Finally, all participants will fill out questionnaires assessing characteristics at baseline, depressive symptomatology, functioning, empowerment, and questionnaires necessary for cost-effectiveness analyses (see Study Parameters section).

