#### Randomization

Participants will be randomly allocated to the control group or one of two ESM intervention groups (“Do-module” and “Think-module”). Randomization (allocation ratio 1:1:1) will be stratified per treatment location according to the duration of antidepressant pharmacotherapy (new/switch vs. maintenance, i.e., receiving antidepressant or mood stabilizing medication for less vs. longer than 8 weeks prior to study entry), and current psychotherapy (yes or no). For these different strata, separate blocks with an allocation sequence of six with an equal condition distribution will be created using an online randomization tool (https://www.random.org/lists). Thus, each of the three conditions will be present twice in a block of six. The allocation will be implemented by using sequentially numbered sealed envelopes (i.e., one pile of envelopes for each stratum). The allocation will be done during the introduction session, by team members who do not have access to the allocation sequence. Participants and research assistants are obviously not blind to treatment. Practitioners are not blind to treatment per se; participants decide themselves whether they want to discuss their feedback reports with their (future) therapist.

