### Missing data

Participants who drop-out during the intervention phase will be asked to fill out the follow-up outcome questionnaires. Participants who complete less than 75% of the ESM measurements during the intervention period, will receive descriptive feedback in their final report but not feedback based on statistical models. Analyses will be performed to examine whether the attrition rate relates to participants’ demographic characteristics and levels of depression. Missing data will be imputed by means of multiple imputation.

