There are a couple of methodological issues that should be considered beforehand. First, as participants need to be motivated to fill out 5 measurements per day for 28 days, the findings may not be generalizable to all depressed patients. In a comparable ESM study, 39% of the invited patients declined to participate [15]. That said, generalizability issues play a role in virtually all intervention studies, and this response rate is comparable to other RCTs in patients with depression (e.g., [49]). Once enrolled, 86% of the depressed participants completed the 6-weeks intervention period in the above-mentioned study [15], indicating that ESM was feasible and acceptable for the majority of depressed patients. Second, the time between the ZELF-i intervention and the start of the regular treatment will not be the same across participants, because waiting list periods vary across time and treatment locations. We will examine the impact of this variation in our analyses. Third, there could be differences between the participating mental health care institutions in the degree to which ZELF-i is accepted by the practitioners and integrated in care as usual. Therefore, we will explore potential differences in the added value of ZELF-i between the different locations. Lastly, we cannot exclude there will be a potential beneficial effect of the extra attention that participants in the intervention groups receive compared to the control group. However, we deemed a sham condition in which participants fill out irrelevant questionnaires too demanding for patients. Furthermore, the extra face-to-face contact is minimal compared to previous research [15]; participants in the intervention groups only have one extra appointment with a research assistant (debriefing) compared to the control group.

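### The efficacy models adjust for the observed gap between starting ZELF-i and starting regular treatment, which generally arises after randomisation and is undefined for anyone who never starts treatment

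*Protocol article*

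**What the plan says.** All references are to the protocol article.

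- **Model** (Efficacy of the ESM-modules): "multilevel regression analyses will be used with the two-way interaction between time (in weeks) and treatment allocation as fixed effects", with a random intercept and a random slope for time. The section says the effects of time, of group and of their interaction will be examined separately, and that similar analyses will be run for NEL and OQ-45.
- **Covariate** (same section): to allow for "individual differences regarding the time interval between the start date of the participation in ZELF-i and the start date of the treatment", "a covariate “start date treatment – start date ZELF-i” will be included in the analyses". No interaction of this covariate with time is stated.
- **Allocation** (Introduction session and baseline measurement): "After the informed consent procedure, participants will be randomly allocated to the control group or one of two ESM intervention groups". The Randomization section says participants are not blind and practitioners are not necessarily blind.
- **Regular treatment** (Participants): it begins when available, and "the start of regular treatment will not be postponed until participation in ZELF-i finishes". Inclusion requires an indication for depression treatment, not that treatment begins.
- **Stratifiers** (Randomization): treatment location, duration of antidepressant medication, and "current psychotherapy (yes or no").
- **Missing data**: "Missing data will be imputed by means of multiple imputation". This is a general sentence that does not mention the covariate.
- **Discussion**: "the time between the ZELF-i intervention and the start of the regular treatment will not be the same across participants". The variation is put down to waiting lists that differ by time and location, and its impact is to be examined in the analyses.

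**The concern.** An efficacy model in a randomised trial should adjust only for what was fixed before allocation. Here one of the two dates that define the covariate usually falls after allocation, during or after the 28 days of monitoring. Participants know their arm, and the intervention aims to strengthen self-management, so it could alter when, or whether, someone takes up care. Severity could also influence both the timing of care and the outcome. Adjusting for the interval could then remove part of the effect of allocation and introduce confounding that randomisation had excluded. The estimate would no longer be the total effect of adding ESM to usual care, which is the stated aim.

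The second difficulty is definition. A participant who never starts treatment has no interval. For a participant already in psychotherapy at entry, it is unclear whether that counts as the treatment in question. If it does, the interval is negative and was fixed before randomisation. If it does not, the value depends on a later start. Leaving out participants without a value breaks the randomised comparison, because not starting care may itself depend on response. Imputing a value supplies a date for an event that did not occur.

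**Working it through.** **1. Order of events.** Consent, then allocation at the introduction session, then 28 days of ESM. Regular treatment starts whenever a place is available. The interval is therefore generally a post-randomisation variable. The exception is a participant whose relevant treatment was already running at entry.

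**2. What a plain main effect does.** Take complete data at common visit times and a random intercept and slope. Each person then contributes a fitted intercept and a fitted slope. The intercepts are regressed on group and interval, the slopes on group alone. Because the regressors for the slope are a subset of those for the intercept, generalised least squares gives the same group difference in slope with or without the interval. I confirmed this identity numerically. Only the group main effect moves.

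**3. Simulation under assumed values** (two arms of 50, six visits, 60 runs per scenario, direct ESM effect on slope set at -0.10 points per week). Time-by-group estimates:

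| ESM arm starts treatment | No interval | Interval as main effect | Interval × time |
|---|---|---|---|
| 3 weeks later | -0.050 | -0.050 | -0.085 |
| 3 weeks earlier | -0.141 | -0.141 | -0.105 |

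The main effect changes nothing. The interaction moves the estimate away from the total effect of allocation and towards the assumed direct effect: by -0.085 - (-0.050) = -0.035 in the first row and -0.105 - (-0.141) = +0.036 in the second. Some fits gave convergence warnings, so this shows direction only.

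**4. Leaving out non-starters.** With 10% (control) and 20% (ESM) improving non-starters removed, the estimate moved from -0.104 to -0.094. That shift of 0.010 is small against a Monte Carlo standard error of about 0.006.

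**5. Loss of power if non-starters are dropped.** The protocol states 85% power for 3 points with 40 per group, alpha 0.05 and an intraclass correlation of 0.6. It gives no SD, so the figure cannot be reproduced from its inputs alone. For a two-sided test of change,

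SD of change = SD × √(2(1 - 0.6)); power = Φ(3 / (SD of change × √(2/n)) - 1.96).

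An SD of about 5 matches the stated figure: SD of change = 5 × √0.8 = 4.47; 3 / (4.47 × √(2/40)) = 3.00; Φ(3.00 - 1.96) = 85.1%. Holding that SD fixed:

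| Completers without a start date (assumed) | n per arm | Power for 3 points |
|---|---|---|
| 0% | 40 | 85% |
| 5% | 38 | 83% |
| 10% | 36 | 81% |
| 20% | 32 | 77% |
| 30% | 28 | 71% |

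The protocol gives no count of non-starters. A model without the interval keeps everyone.

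**The case against.** The strongest defence has three parts.

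**The interval is administrative.** The Discussion attributes it to waiting lists, treatment starts on availability, and researchers do not send feedback reports to therapists. No section says ESM participants postpone, decline or press for care. This stands: dependence on arm is possible in an open-label trial, but not shown. It does not rescue the covariate, because a purely administrative wait is balanced by randomisation and validity does not require adjusting for it.

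**The efficacy contrast is untouched.** As the covariate is written, with complete data, the time-by-group term does not change. This stands too, and limits the harm. A reader might infer that adjustment creates a spurious ESM effect of fixed size. For example, suppose severity shortens the wait by 2 weeks and raises the score by 6 points per SD, with 4 weeks of other variation in the wait. A single-time-point regression then has an interval coefficient of -12/(4 + 16) = -0.6 points per week. A shift of 1–2 weeks between arms yields about 0.6–1.2 points with no true effect. That does not carry over: the inputs are invented, and the trial's model contrasts change over six time points. In that model the distortion falls on the group main effect.

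**Coding rules belong in an analysis plan.** An article may leave the handling of non-starters to a fuller document, and it does not say that any participant will lack a date. This is fair, so the absence of a rule is not itself the fault. The choice of covariate is stated in the article, and it creates the need for such a rule.

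**Conclusion.** The point holds as a design weakness that should be fixed. The protocol commits its efficacy models to a covariate that generally arises after open-label allocation and is undefined for anyone who never starts treatment.

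- **If waiting lists alone drive the interval:** validity does not require the adjustment.
- **If allocation affects it:** adjustment distorts the group main effect, which the protocol says it will examine. The time-by-group contrast is affected as well if the interval is interacted with time, or if participants without a start date are dropped or given an imputed one.
- **As a plain main effect with complete data:** the time-by-group contrast is unchanged, so the covariate also fails to account for different time courses.

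The documents support no figure for the bias. The simulated shifts and the fall in power to 83–71% rest on assumed delays, assumed proportions of 5–30% without a start date, and an SD of about 5 inferred from the stated power. It would go too far to say that the primary estimate is biased, or that participants without a start date are certain to occur.

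**What to change.** 1. Leave the observed interval out of the primary models for IDS-SR, OQ-45 and NEL.
2. Adjust only for pre-randomisation factors, such as the existing stratifiers: location, antidepressant duration and current psychotherapy.
3. Report by arm the distribution of the interval and the proportion not starting treatment.
4. Use the interval only in an analysis labelled supportive or exploratory. State there how non-starters and participants already in treatment at entry are handled, and whether the interval is interacted with time. This still meets the Discussion's commitment to examine the impact of the variation.

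The cost is a sentence or two in the analysis plan, settled before data by arm are seen. No added recruitment or visits are needed, and no randomised participant is lost for want of a start date.

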#### Cost-effectiveness of the ESM-modules

Self-report instruments were completed assessing costs (TIC-P), depressive symptoms (IDS-SR) and quality of life (Euroqol-5D). First, a cost-effectiveness analysis will be performed with the IDS-SR as primary outcome measure. That is, cost effectiveness will be expressed in terms of a ratio where the denominator is a gain in health operationalized as a decrease in depressive symptomatology and the numerator is the cost associated with the health gain (i.e., direct (medical) costs and indirect (productivity losses) costs) assessed during the ESM and follow-up period. The incremental cost-effectiveness ratio will be determined on the basis of incremental costs and effects of ZELF-i (Do-module and Think-module) compared to usual care. Second, a costs-utility analysis will be performed with quality adjusted life years as the primary outcome measure (based on the EuroQol-5D-3 L, a generic, self-report instrument).

#### Patient-experienced utility of the ESM-modules

The patient-experienced utility of the ESM-modules will be analysed in two ways: quantitatively in all participants in the ESM arms through an evaluation questionnaire, and qualitatively through in-depth semi-structured interviews in a subsample. Quantitative data will be presented using descriptive statistics (mean, standard deviation). Two sample t-tests (or a non-parametric variant) will be used to examine differences between participants in the Do-module and Think-module. Qualitative research produces textual data in the form of transcripts and observational field notes, which will be explored inductively using content analysis to generate categories and explanations [25]. For the interviews, a topic list has been created by the researchers. After 4 interviews (2 Do-module, 2 Think-module), this topic list will be reviewed and newly collected issues will be incorporated according to interim analysis [25]. The adjusted topic list will be used for data collection in the successive interviews [48]. This has the advantage that the researchers can refine their questions and stay open to new relevant themes and experiences, which could be in contradiction to previously reported experiences [25]. Data collection and data analysis will be continued until no new themes emerge from the data (i.e., data saturation has been reached).

### Missing data

Participants who drop-out during the intervention phase will be asked to fill out the follow-up outcome questionnaires. Participants who complete less than 75% of the ESM measurements during the intervention period, will receive descriptive feedback in their final report but not feedback based on statistical models. Analyses will be performed to examine whether the attrition rate relates to participants’ demographic characteristics and levels of depression. Missing data will be imputed by means of multiple imputation.

## Discussion

Recent studies have suggested that ESM may be an effective therapeutic tool for patients with depression [11], which calls for further research in regular outpatient care. The present pragmatic RCT will be the first to examine the efficacy of self-monitoring and personalized feedback as a stepping stone for the treatment of depressive complaints in terms of added impact on depressive symptomatology, empowerment and social functioning. By starting directly after intake with ESM, we hope that patients can make the most out of common wait list periods, and commence subsequent treatment programs with a kick-start. ZELF-i is also the first study to evaluate two different ESM intervention modules targeted at both of depression’s core symptoms (ESM “Do-module” and ESM “Think-module”), which will harbor knowledge about what type of ESM-derived personalized feedback is most effective. Lastly, it is the first study that uses a combination of qualitative and quantitative methods to evaluate the patient-experienced utility of ESM with personalized feedback as an intervention for depression. Thus, the proposed study could provide more definitive answers regarding the added value of ESM as a therapeutic tool for depression and potentially improve psychiatric care for depression.

There are a couple of methodological issues that should be considered beforehand. First, as participants need to be motivated to fill out 5 measurements per day for 28 days, the findings may not be generalizable to all depressed patients. In a comparable ESM study, 39% of the invited patients declined to participate [15]. That said, generalizability issues play a role in virtually all intervention studies, and this response rate is comparable to other RCTs in patients with depression (e.g., [49]). Once enrolled, 86% of the depressed participants completed the 6-weeks intervention period in the above-mentioned study [15], indicating that ESM was feasible and acceptable for the majority of depressed patients. Second, the time between the ZELF-i intervention and the start of the regular treatment will not be the same across participants, because waiting list periods vary across time and treatment locations. We will examine the impact of this variation in our analyses. Third, there could be differences between the participating mental health care institutions in the degree to which ZELF-i is accepted by the practitioners and integrated in care as usual. Therefore, we will explore potential differences in the added value of ZELF-i between the different locations. Lastly, we cannot exclude there will be a potential beneficial effect of the extra attention that participants in the intervention groups receive compared to the control group. However, we deemed a sham condition in which participants fill out irrelevant questionnaires too demanding for patients. Furthermore, the extra face-to-face contact is minimal compared to previous research [15]; participants in the intervention groups only have one extra appointment with a research assistant (debriefing) compared to the control group.

